#### **4.4.2.4      *Randomized, Double-blind Phase***

The randomized, double-blind phase of the MIT is designed to test the efficacy of 16 weeks of chronic sildenafil therapy on exercise endurance (6MW distance) and right ventricular systolic pressure (RVSp) in patients with PH and SCD. Randomization of patients meeting inclusion criteria will be stratified in two subgroups according to TRV ( $TRV \geq 2.7$ - $2.9$  m/s and  $TRV \geq 3.0$  m/s); approximately 33 individuals will be randomized to each of the four treatment arm/PH strata combinations.

In the event of VOC, ACS or transfusions, all end-point assessments (including hemodynamic assessment) should be performed  $14 \pm 3$  days after resolution of the acute event or transfusion.

All subjects will have their baseline data confirmed for eligibility prior to randomization. Those qualifying subjects with TRVs between 2.7 m/s and 2.9 m/s will proceed to randomization. Whereas qualifying subjects with  $TRV \geq 3.0$  m/s will next undergo the RHC procedure; those subjects with qualifying wedge pressures will then proceed to randomization. Subjects will be randomized to receive sildenafil 20 mg by mouth (PO) or placebo (matching in pill color and size) three times a day (TID). Study drug will be issued on an outpatient basis for six weeks with the dosage increased to 40 mg TID for four weeks and then increased to 80 mg TID for six weeks.

A peak dose of 80 mg TID was chosen to match our initial open label experience with sildenafil. This is based on the role of hemolysis-associated decreased NO bioavailability in the pathogenesis of pulmonary hypertension associated with sickle cell disease.

The dosing regimen was designed to achieve the following 2 objectives:

1. Minimize sildenafil related adverse effects such as headache and facial/periorbital edema through gradual dose escalation
2. Provide the ability to evaluate the relative efficacy of different sildenafil doses on functional capacity and pulmonary artery pressures as evaluated by echocardiogram

Clinical follow-up will occur at weeks  $6 \pm 1$ ,  $10 \pm 1$ , and  $16 \pm 1$  or EOS, with the following procedures/tests:

- History
- Physical exam and vital signs
- Adverse event monitoring
- Concomitant medications
- Venous blood will be obtained for CBC, standard chemistries
- Pregnancy test
- Venous blood will be obtained for NT-pro Brain Natriuretic Peptide levels and other specialty biomarkers to be run centrally at the NIH

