- Emergency department visits, outpatient/day hospital visits and hospital admissions for sickle cell disease and those for complications of PH will be recorded
- Six-minute walk (with assessment of Borg dyspnea index, and NYHA/WHO functional class) 1-2 hours after taking the morning dose of study drug
- Echocardiogram with assessment of TRV LV and RV function 1-2 hours after taking the morning dose of study drug. All echocardiograms should be performed at least one hour after 6MW test. EXCEPTION NOTE: Echocardiogram will not be assessed at week  $10 \pm 1$
- Study drug compliance and daily pain assessment using the BPI --evaluated by subject for one week between each follow-up visit

End of the double-blind phase visit (week  $16 \pm 1$ ) will also include:

- In subjects with an initial study entry TRV  $\geq 3.0$  m/s a second right heart catheterization
- Quality of life assessment using SF-36 Quality of Life form (ages 14-adult) or Peds-QL (ages 12-13)

In subjects with TRV  $\geq 3.0$  m/s clinically indicated studies (according to accepted guidelines) for the work-up of subjects with pulmonary hypertension (PH) can be ordered at the discretion of treating clinicians. These studies could include:

- Collagen vascular screening tests (e.g., ANA, anti-centromere antibodies, anti SCL-70, antiphospholipid antibodies)
- Ventilation perfusion scan
- Chest X-ray (required for all MIT subjects at baseline), CT of chest
- Overnight pulse oximetry
- Spirometry with bronchodilation

- Lung volume
- Diffusing capacity for CO

Efficacy assessments will be done at peak dose (i.e., study medication should be taken 1-2 hours before measurements) when subjects are in a steady state.

A subset of clinical outcomes will be adjudicated by a blinded panel of experts. Adjudicated outcomes include: ACS, right heart failure, and clinical worsening.

Records of study drug used, dosages administered, and intervals between visits are kept during the study. Study drug accountability is performed on an ongoing basis by the study personnel and checked by the clinical research associate (CRA) during site visits and at the completion of the study. Subjects are asked to return all unused study drug at each visit.

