## 6 RANDOMIZATION AND BLINDING

The study will randomize 132 subjects.

After successful qualification of their baseline data and the completion of the RHC procedure (for subjects with TRV  $\geq 3.0$ ), subjects will be randomized to one of two treatment arms by the internet based, secure RhoRAND™ system provided by the Data Coordinating Center (DCC). Subjects in Arm 1 will receive sildenafil. Subjects in Arm 2 will receive oral placebo. A computer-generated, adaptive randomization schema will be used to allocate subjects 1:1 between the two treatment arms. Randomization will be stratified by site and TRV stratum ( $2.7 \text{ m/s} \leq \text{TRV} < 3.0 \text{ m/s}$  versus  $\text{TRV} \geq 3.0 \text{ m/s}$ ). As the number of stratification factors is rather large ( $9 \times 2 \times 2$ ), many strata may have fewer subjects than the block size, and a good balance can no longer be guaranteed for all of them^34. As a result, the use of a traditional stratified, blocked randomization schedule could lead to significant imbalance in treatment allocations, both across the study and within the various strata. In order to increase the likelihood of balance in treatment allocations, subjects will be randomized using the standardized range variation of the sequential allocation algorithm of Pocock and Simon, a minimization method. This method attempts to achieve treatment balance on several subject characteristics (i.e., site and TRV stratum in this study) simultaneously – not within separate strata. Minimization

consists of biasing the treatment allocation so as to minimize the total imbalance between the treatment groups on some scale. The order of entry of the subjects to the various sites and in the various prognostic groups is assumed to be random. As minimization is a dynamic method that uses information on subjects already entered to allocate treatment to the next subject, and thus a continuous updating of the information related to previous treatment allocations is required, a centralized randomization system will be used.

The unmasked statistician will monitor the balance of treatment assignments across subjects on anticoagulants (defined as vitamin K antagonists and heparin). If a significant imbalance is detected, anticoagulant use will be added as stratification factor in the randomization.

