## **7.2 Dose Modification or Discontinuation Due to Expected Adverse Events: Headache or Facial/skin Edema**

Dose adjustment instructions for symptomatic/dose limiting headache or facial/skin edema sufficient to warrant discontinuation of the drug (only for symptoms that are severe enough as described by subject or physician to warrant holding the drug) are provided herein.

1. If present during initial dose (20 mg) hold for one day and rechallenge, if symptoms occur upon rechallenge discontinue drug. Data collection should continue for such subjects to the extent possible.

2. If present during dose escalation (40 or 80 mg) hold drug for one day and restart at previously tolerated dose for one week. If symptoms recur, discontinue drug but continue to follow subject for collection of safety and other data. If tolerated for one week increase dose to desired level as dictated by protocol. If symptoms recur upon second increase hold drug for one day and drop dose to previously tolerated dose for the duration of the trial.

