### 11.2.2 Secondary Efficacy Endpoints

The objectives of the analyses of the *secondary efficacy endpoints* are to:

- Evaluate descriptively and with model based estimation and informal hypothesis tests the effects of sildenafil therapy on sickle cell patients diagnosed with PH on multiple outcome measures including hemodynamic parameters, standard clinical measures of PH, and quality of life measurements
- Gain through descriptive and exploratory analyses a better understanding of what clinical and demographic factors might affect the efficacy of sildenafil for PH in this population

- Provide age and gender prevalence estimates for pulmonary hypertension in sickle cell patients

Secondary efficacy endpoints of the main trial will be analyzed as follows:

- Continuous outcome measures (e.g. hemodynamic parameters (RVSP), change in TRV, change in 6MW distance on sildenafil 20 mg vs. 40 mg and 80 mg in the group receiving active drug during the placebo controlled study) will generally be analyzed based on a combination of descriptive summaries and model-based analyses using models like that described for the primary endpoint analysis. At-visit-values and change from baseline values will be analyzed and reported. Descriptive, model based analyses will then be generated based on both analysis of variance type models (ANOVA) and analysis of covariance type models (ANCOVA) that control for both demographic and clinical parameters of interest (e.g. baseline NYHA/WHO functional class or baseline Borg dyspnea).
- Time to clinical deterioration of PH will be based on decisions of a blinded adjudication panel (see Section 9.2.4) and will be assessed by Kaplan-Meier methodology. These assessments will utilize log rank tests based on the Kaplan-Meier estimates used to test for differences between the two treatment groups. For this time to event outcome, Cox proportional hazards models will be used to assess whether clinical factors (e.g., TRV stratum, baseline NYHA/WHO functional class) act as confounders or effect modifiers of the treatment effect.

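### The titration scheme cannot show the relative efficacy of sildenafil doses: dose and time on treatment coincide, the planned comparison leaves out placebo, and the 40 mg step has no echocardiogram

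*Protocol*

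**What the plan says.** Section 4.4.2.4 gives two reasons for the dosing regimen. The second is to "Provide the ability to evaluate the relative efficacy of different sildenafil doses on functional capacity and pulmonary artery pressures as evaluated by echocardiogram".

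The same section starts every active subject on 20 mg TID for six weeks, with the "dosage increased to 40 mg TID for four weeks and then increased to 80 mg TID for six weeks"; section 8 repeats this schedule. Visits fall at Weeks 6, 10 and 16, the end of each step. Section 6 describes two arms only: an "adaptive randomization schema will be used to allocate subjects 1:1 between the two treatment arms". Nobody is randomized to a dose or to a sequence of doses.

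Section 11.2.2 lists, among the continuous secondary outcomes, "change in 6MW distance on sildenafil 20 mg vs. 40 mg and 80 mg in the group receiving active drug". It names no placebo contrast for this comparison.

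On echocardiography, the visit list in section 4.4.2.4 carries the exception "Echocardiogram will not be assessed at week" 10, and the echo row of Table 4 is blank there.

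The protocol allows one departure from the common schedule. Under section 7.2, a subject with repeated dose-limiting headache or edema after escalation may "drop dose to previously tolerated dose for the duration of the trial".

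**The concern.** The objective is an affirmative claim about what the design can deliver. To compare doses, something other than dose must be held fixed or balanced. Here 20 mg always means Weeks 0 to 6, 40 mg Weeks 6 to 10 and 80 mg Weeks 10 to 16. A difference between steps within the sildenafil arm therefore mixes the effect of the higher dose, the effect of longer exposure, and whatever would have happened over those weeks anyway.

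The concurrent placebo arm walks at the same visits and could remove the last of these, but section 11.2.2 does not use it for the dose comparison. For pulmonary pressure, the objective names an outcome that is not measured at the middle step.

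The stake is interpretive. Section 2.3 cites a randomized parallel-dose trial of 20, 40 and 80 mg in which 6MW benefit showed no relation to dose. A rise across visits in this trial, labelled by dose, could seem to contradict that evidence through the passage of time alone.

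**Working it through.** **Starting point.** The protocol gives no power or precision figure for the dose comparison. As a check on its sample-size work, a two-sample t-test calculation with the noncentral t reproduces all nine cells of Table 6 (for example 60, 52 and 46 per arm at SD 67 m). The primary sizing is not in question.

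**Identifiability (no numerical assumption needed).** Within the active arm there are three visits, and each has one scheduled dose. A model with an intercept, two visit terms and two dose terms has 1 + 2 + 2 = 5 columns but rank 3, so no dose effect can be separated from visit. Treated as numeric scores, dose (20, 40, 80) and week (6, 10, 16) correlate at 0.997. The reductions under section 7.2 do not help, because subjects held at a lower dose are selected by intolerance.

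**Inputs for an illustration, all from section 11.6.**
- Assumed mean change on sildenafil: 15, 25 and 40 m at Weeks 6, 10 and 16
- Assumed mean change on placebo: 0 m at all three visits
- Within-subject SD: 47.4 m, from the mixed model
- 66 subjects per arm, or 60 before the 10% supplement for dropout

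I assume independent within-subject errors across visits.

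**Within-arm 80 versus 20 mg contrast (Week 16 minus Week 6).**
- SD of the difference = 47.4 × √2 = 67.0 m. (It is close to the 67 m used for the primary endpoint by coincidence; the quantities differ.)
- SE with n = 66: 67.0 / √66 = 8.25 m
- Contrast: 40 − 15 = 25 m, so 25 / 8.25 = 3.03
- Chance of p<0.05 (paired t-test, noncentral t): about 85% with n = 66 and about 81% with n = 60

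These chances are the same whether the 25 m comes from dose, from time on drug, or from both. If it comes wholly from time on drug, they are the chances of a nominally significant dose contrast when no dose effect exists.

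**A drift common to both arms.** The documents give no figure for such a drift, so a range is assumed. It passes one for one into the within-arm contrast:

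| Assumed drift, Week 6 to 16 | Chance of p<0.05, n = 66 |
|---|---|
| 0 m | 5% |
| 5 m | 9% |
| 10 m | 22% |
| 15 m | 43% |
| 20 m | 67% |

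**With placebo subtracted.** The SE of the between-arm difference in the Week 6 to 16 change is 67.0 × √(2/66) = 11.7 m. A 25 m change in effect gives 25 / 11.7 = 2.14, with power about 57%. A drift common to both arms cancels. What remains is the combined effect of higher dose and longer exposure, and placebo data cannot split those.

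**Echocardiography.** Only Week 6 (20 mg) and Week 16 (80 mg) have values. Their within-arm comparison is aliased with time in the same way, and no 40 mg value exists.

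**The case against.** The strongest case against is about consequence. Relative dose efficacy is not among the objectives in the synopsis or section 3, nor in the endpoint list of section 4.4.1. It appears once as a reason for the regimen and once as an example inside a parenthesis. Section 11.2.2 calls the secondary tests informal, and section 11.5.3 makes every p-value except the primary one descriptive. All of this stands and limits the severity. It does not make the contrast identifiable, and the objective remains a claim the design cannot meet.

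It can also be said that placebo is not lost: section 11.2.2 summarises all efficacy measures by treatment group, and the mixed model in section 11.2.1 fits both arms with time as a fixed effect. A reader will see the placebo course. But that model compares treatment groups, states no treatment-by-visit term, and is not what section 11.2.2 applies to the doses. Adding the term could be left to an analysis plan; choosing an active-arm-only contrast is a decision already written here.

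Some stronger readings do not hold:
- A reader might infer that the trial will report a dose-response. No section commits it to that conclusion.
- A reader might assume a definite learning effect. Section 9.2.3 provides a practice walk before screening (waived after a recent documented test) and repeat walks before randomization, and section 11.6 assumes no placebo change. Learning is reduced, though not shown to be zero.
- A reader might count dropout of intolerant subjects as a false dose effect. In a paired comparison the same subjects supply both visits, so dropout limits who is represented rather than shifting the contrast through changing composition.
- On echo, section 11.2.2 spells out the dose comparison for 6MW only. The contradiction lies between the objective and the visit schedule, both in section 4.4.2.4.

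**Conclusion.** The point holds as a should-fix matter of wording and analysis choice. The stated ability to evaluate relative dose efficacy does not exist under this design, for 6MW or for echo pressures, and the active-arm-only comparison includes any time trend. That conclusion follows from the schedule and the randomization alone.

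The percentages are illustrations of size. They rest on an SD of 47.4 m taken from an uncontrolled series in a different form of pulmonary hypertension (12 patients, section 2.3), on independent errors, and on 60 to 66 subjects in the active arm. The drift range is assumed. They are chances of a nominally significant result, not estimates of bias. The primary sildenafil-placebo comparison at Week 16 is not affected, and nothing here should be read as casting doubt on it.

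**What to change.** - **Section 4.4.2.4:** restate the second objective as evaluating the effect at each titration step, saying that dose and duration of treatment are not separable; or delete it. Limit the echo part to Weeks 6 and 16.
- **Section 11.2.2:** replace the active-arm-only dose comparison with sildenafil-minus-placebo differences at Weeks 6, 10 and 16 from a treatment-by-visit model, and state that they will not be interpreted as dose-response.

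The cost is wording and one model term, using data already scheduled for collection. The one loss is precision for the change in effect between steps: an SE of about 11.7 m instead of about 8.3 m under the same assumptions. No change to dosing or visits is proposed.

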#### **4.4 Main Interventional Trial**

##### **4.4.1 Description of Study Endpoints**

The *primary efficacy endpoint* is the change in 6-minute walk (6MW) distance across the 16 weeks of therapy.

The *secondary efficacy endpoints* include the following:

- Hemodynamic parameters (right atrial pressure; pulmonary artery systolic pressure; pulmonary artery diastolic pressure; MPAP; pulmonary capillary wedge pressure; PVR; cardiac output; mixed venous oxygen saturation; systemic systolic, diastolic and mean pressures; SVR; and body surface area indexed values for cardiac output, PVR, and SVR)
- Left and right ventricular systolic and diastolic function
- NYHA/WHO functional class
- Borg dyspnea score
- Time to clinical deterioration of PH
- Clinical outcomes: number of visits to emergency departments; hospitalizations; reasons for hospitalizations; episodes of acute chest syndrome, number of transfusions
- Quality of Life score (SF-36 for ages 14-adult; Peds-QL for ages 12-13)
- Pain score (BPI)

The *safety endpoints* include the following:

- Vital signs, including blood pressure
- Change in physical examination
- Urinalysis
- CBC
- Reticulocyte count
- Peripheral oxygen saturation by pulse oximetry
- AE monitoring

- Baseline history and interim history (including pain history, pain treatment, respiratory symptoms, inpatient or outpatient evaluations, and management of SCD-related complications)
- Concomitant medications monitoring

The *genetic/biomarker assessments* include the following:

- NT-pro Brain Natriuretic Peptide levels (BNP)
- DNA sequencing

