| Ophthalmologic Exam                                                                                                                                                                                                                                        | X  |                                |                |                     |                                         |
| Chest X-ray                                                                                                                                                                                                                                    | X              |                                |                |                     |                                         |
| O 2 saturation                                                                                                                                                                                                                                  | X              | X                              | X              | X                   |                                         |
| Quality of Life (SF-36 or Peds-QL)                                                                                                                                                                                                                         | X              |                                |                | X                   |                                         |
| Biomarkers (Central Labs, e.g. NT-BNP)                                                                                                                                                                                                                     | X              | X                              | X              | X                   |                                         |
| Symptoms documentation: hospitalizations, ED, Clinic, transfusions, ACS, priapism                                                                                                                                                                          | X              | X                              | X              | X                   |                                         |

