### **9.3.4 Medical History**

At screening, the subject's medical history will be recorded including: previous treatment for SCD, previous ACS events, previous strokes, pain crises frequency and usual management, history of priapism, previous transfusions and reactions to transfusions and to medications.

The subject's interim medical history will be recorded at baseline and every clinic visit of the MIT, focusing on emergency department (ED) visits, day clinic visits, hospitalizations, self-medicated crises, and analgesic usage (see Appendix B for sample data collection tool).

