- The effect of treatment on the categorical measures of Borg dyspnea scale, BPI score, quality of life score, and NYHA/WHO functional class (all ordinal measures), will be examined descriptively. For each of these ordinal measures, both cross-sectional descriptions of the outcome at each time point and shift-tables from baseline will be developed to compare treatment arms descriptively. To generate informal hypothesis tests Mantel-Haenszel procedures will be used to assess for outcome differences at Week 16 and end-of-study controlling for baseline levels of the measure and TRV stratum.
- Differences across treatment groups for the clinical endpoints of death, episodes of acute chest syndrome, emergency department visits, outpatient/day hospital visits, hospitalizations, and transfusions will be analyzed using Fisher's exact test, if the number of events is sufficient. Otherwise, these data will be summarized by treatment group.

In the final report, all continuous efficacy measures (e.g. 6MW distance, hemodynamic parameters, quality of life assessments) will be summarized by N, mean, median, standard deviation, minimum, and maximum. Statistics used to summarize categorical variables (e.g. NYHA/WHO functional class) will include number and percent in each category. All efficacy measures will be summarized by treatment group, TRV strata, and treatment by TRV strata.

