## **13 SAFETY EVALUATIONS AND REPORTING PLAN**

### **13.1 Safety Assessments Overview**

During the initial screening phase, subjects will be monitored for adverse events and serious adverse events.

Subjects in the double-blind phase of the Main Intervention Trial will have routine evaluations at weeks 6, 10 and 16. At each visit, subjects and/or their parents will be queried regarding recent medical events or procedures. Specific events will be documented at each visit to ascertain the nature and treatment of the event, including pain crises, episodes of acute chest syndrome, transfusions, and hospital admissions. These events and diagnoses will be followed up by the nurse coordinator, who will review

hospital charts, medical records, and office visit records for documentation in the follow-up visit forms in the CRF. Additionally, clinical laboratory data (specified elsewhere in the protocol) will be assessed to evaluate safety concerns. Subjects will continue receiving the same regimen until they have been followed for 16 weeks or until they have discontinued from the study.

During the open-label follow-up phase, subjects will be monitored for adverse events and serious adverse events at every 1-3 months, based on each site's standard practice.

Subjects in the Observational Follow-up Study may be contacted every 6-12 months and asked to report on their experiences in relation to a pre-designated list of clinical events only. These clinical events are noted in section 9.2.

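### Section 4.4.2.4 ties the recording of ED visits, day-hospital visits and admissions to sickle cell disease or PH, while the endpoint, its analysis and the other collection texts state no cause limit

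*Protocol*

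**What the plan says.** The secondary efficacy endpoints in Protocol section 4.4.1 include "Clinical outcomes: number of visits to emergency departments; hospitalizations; reasons for hospitalizations; episodes of acute chest syndrome, number of transfusions". No cause is specified, and the reason for a hospitalization is itself an outcome. Section 11.2.2 compares the arms, also without naming a cause: "Differences across treatment groups for the clinical endpoints of death, episodes of acute chest syndrome, emergency department visits, outpatient/day hospital visits, hospitalizations, and transfusions" are to be tested with Fisher's exact test if there are enough events, and otherwise summarized by arm.

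Four places describe collection during the double-blind phase:

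- Section 4.4.2.4, in the list of procedures for weeks 6, 10 and 16: "Emergency department visits, outpatient/day hospital visits and hospital admissions for sickle cell disease and those for complications of PH will be recorded".
- Table 4, at baseline and weeks 6, 10 and 16: "Symptoms documentation: hospitalizations, ED, Clinic, transfusions, ACS, priapism".
- Section 9.3.4, interim history at baseline and every MIT clinic visit: "focusing on emergency department (ED) visits, day clinic visits, hospitalizations, self-medicated crises, and analgesic usage".
- Section 13.1, events documented at each visit and followed up in hospital charts and other records for the CRF: "including pain crises, episodes of acute chest syndrome, transfusions, and hospital admissions".

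Only the first of these mentions a cause for the contact.

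**The concern.** Naming two causes in 4.4.2.4 has little purpose unless it limits what is recorded. Read that way, a subject seen in an ED for headache, hypotension or a visual change counts under 4.4.1, 11.2.2, Table 4 and 9.3.4, but not under 4.4.2.4. Two sites could each follow a passage of the protocol and report different numbers for the same subject.

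Two things would be at stake. First, a form built on 4.4.2.4 would undercount contacts for other causes. Where those are drug effects, the missing contacts would tend to be in the sildenafil arm. Second, each contact would need a site judgement of cause, which the protocol does not make easy. Priapism requiring intervention, for example, is listed in section 13.7.2 both under sickle cell anemia and under sildenafil.

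**Working it through.** **Comparison of the texts.** There is no stated figure to reproduce, because the protocol gives no event rate and no power for this endpoint. The check is therefore mainly a reading of each place side by side.

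| Place | Role | Contacts named | Cause limit |
|---|---|---|---|
| 4.4.1 | endpoint | ED visits, hospitalizations, reasons for hospitalization | none stated |
| 11.2.2 | analysis | ED, outpatient/day hospital, hospitalizations | none stated |
| 4.4.2.4 | collection | ED, outpatient/day hospital, admissions | sickle cell disease and PH complications |
| Table 4 | collection | hospitalizations, ED, clinic | none stated |
| 9.3.4 | collection | ED, day clinic, hospitalizations | none stated |
| 13.1 | collection | hospital admissions | none stated |

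Section 4.4.2.4 is the only entry with a cause. Its grammar also leaves open whether the cause qualifies all three kinds of contact or only the admissions. No passage says which text governs the count.

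**Illustration of size.** The only input from the protocol is the arm size, 66 (section 11.6). The rates are assumptions:

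- b = share of subjects with at least one sickle cell or PH contact, equal in both arms: 20% or 40%.
- t = share of the remaining sildenafil subjects with a contact for a drug effect only: 5% or 10%; none on placebo.

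The unrestricted share on sildenafil is p = b + (1 - b)t. A count restricted by cause shows b in both arms, a difference of zero, so it hides d = p - b = (1 - b)t. The standard error of the unrestricted difference is SE = sqrt{[p(1 - p) + b(1 - b)]/66}.

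| b | t | p | d (points) | SE (points) | d/SE |
|---|---|---|---|---|---|
| 20% | 5% | 24% | 4.0 | 7.2 | 0.56 |
| 20% | 10% | 28% | 8.0 | 7.4 | 1.08 |
| 40% | 5% | 43% | 3.0 | 8.6 | 0.35 |
| 40% | 10% | 46% | 6.0 | 8.6 | 0.70 |

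For the first row, d = 0.80 × 0.05 = 0.04 and SE = sqrt[(0.24 × 0.76 + 0.20 × 0.80)/66] = sqrt(0.3424/66) = 0.072.

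**What the planned test would see.** The probability that Fisher's exact test on the unrestricted count gives p < 0.05 was found by summing over all outcomes of two binomials with 66 per arm, for b of 20%, 35% and 50% and t of 3%, 5% and 10%. It runs from about 0.03 to 0.14, against about 0.03 with no true difference. Under these assumptions the test would seldom flag the difference even with complete recording. What would change is the reported descriptive difference.

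**The case against.** A reader might infer that contacts caused by drug toxicity are left out of the comparison and that the result is therefore biased in favour of sildenafil. The documents do not support that as a statement of fact:

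- Section 4.4.2.4 does not say *only*. Table 4 and 9.3.4 collect ED visits and hospitalizations without a cause limit, 9.3.4 also covers day clinic visits, and 13.1 covers admissions. Loss of these contacts follows only if the narrow reading of one bullet overrides the rest.
- It would also be wrong to say that ED and day-hospital visits have no other record. Table 4 and 9.3.4 provide one for ED visits, and 9.3.4 does for day clinic visits.
- Toxicity is followed elsewhere. An adverse event requiring hospitalization is an SAE whatever its cause (13.2.2) and goes on the CRF (13.6). Section 11.3 compares adverse events that occur in more than 10% of subjects.
- The protocol never calls the endpoint all-cause; it leaves the cause unspecified. A disease-specific count would be a legitimate, different endpoint.
- The protocol has no figure for contacts due to drug effects. Its nearest ones measure other things: headache in 16% against 4% in the flexible-dose studies (Table 8), discontinuation for adverse events of 2.5% against 2.3% (12.3.2.2), and 2 of 22 sickle cell patients stopping for headache without a control group (12.3.2.4).

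All of this stands, and it confines the point to an inconsistency with a conditional consequence. It does not remove the inconsistency. The collection texts disagree with each other and none is given precedence. The adverse event analyses in 11.3 count events, so a visit without admission may appear there as an event term but not as a contact.

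**Conclusion.** The protocol does not settle which contacts count for this secondary endpoint: 4.4.2.4 names causes, and 4.4.1, 11.2.2, Table 4, 9.3.4 and 13.1 do not. If 4.4.2.4 is followed, contacts for other causes would be undercounted. The descriptive difference between arms could then shift by about 3 to 8 percentage points on the assumed rates. That range rests wholly on those rates and on such contacts occurring only on sildenafil; the protocol's own figures can neither confirm nor narrow it.

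Section 11.5.3 makes p-values outside the primary test descriptive, so the primary analysis and its error rate are unaffected. Severity: minor. It still deserves settling before data collection. A cause-limited count can be derived later from complete records, but contacts that were never recorded cannot be restored by any analysis plan.

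**What to change.** Remove the cause qualifier from the bullet in 4.4.2.4, so that every ED visit, outpatient/day-hospital visit and inpatient admission is recorded with its reason, in line with 4.4.1, Table 4 and 9.3.4. Analyse the contacts without a cause limit, as 11.2.2 reads, and tabulate sickle cell, PH and other causes separately. The reason field also supplies the reasons for hospitalization that 4.4.1 lists as an outcome, and it keeps the disease-specific count available.

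If the sponsor does intend a disease-specific endpoint, 4.4.1 and 11.2.2 should say so, with a rule for assigning cause; complete recording would still be preferable. The cost is one sentence, a reason field on the form, and a few more contacts for sites to record.
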